**Table 1. Concentration of ions in intravenous fluids\***

| Strong Ion                           | Plasma**         | Plasmalyte | Saline(0.9%) | Hartmann's |
|--------------------------------------|------------------|------------|--------------|------------|
| Sodium (Na + ), meq/L     | 140 (135 to 145) | 140        | 150          | 150        |
| Chloride (Cl  ), meq/L   | 102 (98 to 108)  | 98         | 150          | 150        |
| Potassium (K + ), meq/L   | 4.0 (3.5 to 5.0) | 5          | 0            | 0          |
| Calcium (Ca 2+ ), meq/L   | 2.4 (2.3 to 2.6) | 0          | 0            | 0          |
| Magnesium (Mg 2+ ), meq/L | 2.0 (1.4 to 2.4) | 3.0        | 0            | 0          |
| Acetate, meq/L                       | 0                | 27         | 0            | 0          |
| Gluconate meq/L                      | 0                | 23         | 0            | 0          |
| Lactate, meq/L                       | 1.0 (0.5 to 2.0) | 0          | 0            | 0          |
| Strong Ion Difference meq/L          | 44               | 49         | 0            | 0          |

\*All fluids are manufactured by Baxter Healthcare, Toongabie, NSW.

\*\*Median, Reference Range

## FEASIBILITY AT AUSTIN HOSPITAL

The departments of anaesthesia and Intensive Care at Austin Hospital have completed 6 fluid intervention studies, and currently there is one fluid intervention study still underway in the setting of renal transplantation.

### Fluid intervention in liver resection

Recently, the authors completed a multicentre randomized double-blind controlled multicentre study of Plasmalyte vs. Hartmann's solution in patients receiving liver resection. Participants were randomized to Plasmalyte or Hartmann's solution for intraoperative fluid intervention. Primary outcome: base-excess immediately after surgery. Secondary outcomes: lactate levels, strong-ion-difference (SID), total weak acids, net-unmeasured-ions, changes in liver enzymes, perioperative complications and duration of hospital stay. Results: 60 participants were recruited from 4 tertiary-level hospitals. Both groups were matched according to baseline characteristics, extent of resection, and surgery duration. There were no differences in the volume of trial fluid used, perioperative fluid balance, or urine output. Plasmalyte was not inferior to Hartmann's for the primary endpoint. Plasmalyte base-excess was 0.8mmol/L greater (95%CI: -0.4 to 2.0;P=0.18). This was associated with hyperchloraemia (Difference 1.7mmol/L, 95%CI: 0.2 to 3.2mmol/L, p=0.03) and hyperlactaemia (Difference 0.8mmol/L, 95%CI: 0.2 to 1.3mmol/L;P=0.01) in the Hartmann's group. In the Hartmann's group 23 patients (77%) had a lactate above the reference range compared to 14 patients (47%) in the Plasmalyte group, P=0.02. Complications were more frequent in the Hartmann's Group (56% vs. 20%, 95%CI: 1.3 to 6.1;P=0.007). Median length of hospital stay: 5.9 days vs. 7.8 days (P=0.041) favouring Plasmalyte group.

**The SPLIT Study: Saline (0.9%) vs. Plasma-Lyte® 148 Fluid Intervention Trial in Major Surgery Patients, Version 3, 1st Oct 2014**

Conclusion: For patients undergoing liver resection use of Plasmalyte solution resulted in improved acid base haemostasis, less hyperlactaemia, reduced perioperative complications and a shorter length of hospital stay compared to patients receiving Hartmann's solution.

### **Fluids and cognitive function in healthy volunteers**

In another study, the authors tested the hypothesis that saline infusion would produce greater cognitive changes than Plasmalyte in healthy volunteers. With Ethics Committee approval, we conducted a randomized, cross-over, blinded study of healthy adult volunteers. On separate days participants were randomized to 30 ml/kg over one hour of either saline or Plasmalyte. Plasma chemistry was tested on venous samples. As part of a battery of cognitive tests our primary end point was the reaction time index. We studied 25 participants. Plasma chloride was greater after saline, difference 5.4 mmol/L (95%CI: 4.1 to 6.6 mmol/L,  $P < 0.001$ ) associated with greater metabolic acidosis: base-excess 2.5 mmol/L more negative (95%CI: 1.9 to 3.0 mmol/L more negative,  $P < 0.001$ ). There were no important differences in reaction time index between the two arms of the study. After saline, the mean reaction time index was 411 (SD: 63) msec, and after Plasmalyte was 385 (SD: 55) msec: saline 9 msec slower (95 CI: 12 msec faster to 30 msec slower,  $P = 0.39$ ). None of the other cognitive and mood tests differed. We concluded that despite significant differences in plasma chemistry, reaction times after saline did not differ from reaction times after Plasmalyte. Further, other measures of cognition did not differ. This finding was contrary to our hypothesis. We cannot exclude differences with Hartmann's solution, however, cognitive differences associated with mild hyperchloremic metabolic acidosis seem unlikely.

### **Fluid intervention in cardiac surgery**

The authors have successfully completed 4 fluid intervention studies in the setting of cardiac surgery.

Most recently, we examined the effect of pump prime on acidosis, strong-ion-difference and unmeasured ions during cardiopulmonary bypass in a randomized blinded clinical trial. There are no studies comparing the mechanism of metabolic acidosis during cardiopulmonary bypass (CPB) using Hartmann's solution and Plasmalyte as pump primes, therefore we tested the hypothesis that the effects of these crystalloids on acidosis is a function of their individual strong ion differences (SID) and unmeasured anions. After Ethics approval we performed a randomised blinded study of 38 adult patients undergoing elective CABG or valve replacement requiring CPB. Both groups received a prime solution of 2000mL; one group with anions lactate and chloride (Hartmann's), the other with anions acetate, gluconate and chloride (Plasmalyte). Endpoints were standard base deficit, SID, total weak acids, and strong ion gap (SIG). Serum electrolytes and arterial blood gases were collected at 6 intervals: immediately prior to CPB (T0), then 2min (T1), 5min

**The SPLIT Study: Saline (0.9%) vs. Plasma-Lyte® 148 Fluid Intervention Trial in Major Surgery Patients, Version 3, 1st Oct 2014**

(T2), 10min (T3), 30min (T4), and 60min (T5) post CPB. On delivery of pump prime both groups developed metabolic acidosis – Plasmalyte® (base excess: 0.53mmol/L (T0) to -3.03mmol/L (T1),  $P=0.001$ , Hartmann's; base excess: 0.42mmol/L (T0) to -2.20mmol/L (T1),  $P=0.001$ . Lactate remained unchanged in the Plasmalyte group, however peaked with Hartmann's at 2min: 0.15mmol/L (T0) to 4.5mmol/L (T1),  $P=0.001$ , returning to baseline by 60minutes. There was significant hyperchloraemia with Hartmann's compared to Plasmalyte. The SID with Plasmalyte® increased from 37.6mEq/L (T0) to 40.3mEq/L (T1),  $P=0.001$ , remaining elevated at 60minutes (36.7mEq/L). Conversely with Hartmann's, the SID decreased from 36.3mEq/L (T0) to 31.2mEq/L (T1) and remained decreased at T5 (33.3mEq/L). The SIG increased significantly from T0 to T1 with Plasmalyte® (1.1mEq/L to 11.9mEq/L,  $P=0.001$ ), but marginally with Hartmann's (-0.6mEq/L to 2.0mEq/L). We concluded that the mechanism of acidosis during CPB with Hartmann's solution was due to combination of iatrogenic hyperlactaemia and hyperchloraemia. In contrast the mechanism with Plasmalyte was a production of unmeasured anions, most likely acetate and gluconate.

Second, we previously studied acid-base changes during CPB with polygeline pump prime and defined and quantified the factors, which contribute to metabolic acidosis. Using quantitative biophysical methods, we demonstrated that in patients receiving a pump prime rich in chloride and polygeline, the metabolic acidosis of CPB was mostly due to iatrogenic increases in serum chloride concentration and unmeasured strong anions.

Its development was partially attenuated by iatrogenic hypoalbuminaemia. Changes in lactate concentrations did not play a role in the development of metabolic acidosis in our patients.

Because the development of metabolic acidosis during cardiopulmonary bypass was well recognized but poorly understood, in another study we hypothesized that the delivery of pump prime fluids is primarily responsible for its development. We studied acid-base changes induced by the establishment of CPB using two types of priming fluid (Haemaccel, a polygeline solution, and Ringer's Injection vs. Plasmalyte) using quantitative biophysical approach. Immediately on delivery of pump prime fluids, all patients developed a metabolic acidosis. The decrease in base excess was the same for both primes (4.60 vs. 4.37; not significant). However, the mechanism of metabolic acidosis was different. With the Haemaccel-Ringer's prime, the metabolic acidosis was hyperchloremic, whilst with Plasmalyte, the acidosis was induced by an increase in unmeasured anions, most probably acetate and gluconate, although these were not directly measured. The resolution of these two processes was different because the excretion of chloride was slower than that of the unmeasured anions. This study demonstrated that cardiopulmonary bypass-induced metabolic acidosis was iatrogenic in nature and derived from the effect of pump prime fluid on acid-base balance.

**The SPLIT Study: Saline (0.9%) vs. Plasma-Lyte® 148 Fluid Intervention Trial in Major Surgery Patients, Version 3, 1st Oct 2014**

Finally, we tested the hypothesis that a cardiopulmonary bypass prime with lactate would be associated with less acidosis than a prime with only chloride anions because of differences in the measured strong-ion-difference. We randomised 20 patients to a 1500 ml bypass prime with either a chloride-only solution (Ringer's Injection) or a lactated solution (Hartmann's solution). We found that the chloride-only group had greater acidosis with lower base-excess and pH. Contrary to our hypothesis, however, the difference between the groups was not due to a difference in the measured strong-ion-difference. When the difference in standard base-excess between the groups was greatest, the difference in the measured strong-ion-difference was only very small. There was however, a difference in the net-unmeasured-ions (strong-ion-gap). We concluded that acid-base changes with cardiopulmonary bypass might differ with the prime but that the early differences between chloride-only and lactated primes appear not to be due to differences in the measured strong-ion-difference. We suggested that future studies examine other possible mechanisms including unmeasured ions.

### **Fluid intervention in renal transplantation**

Currently the authors are half way through a randomised trial evaluating the use of either Saline (0.9%) or Plasmalyte solution in patients undergoing renal transplantation. We hypothesised that the balanced crystalloid fluid Plasmalyte, will have more favourable effects on metabolic acidosis and early graft function compared to Saline (0.9%). Adult patients (age > 18 years) undergoing deceased donor renal transplantation (heart-beating or non heart-beating) are included with the primary endpoint being base deficit immediately post surgery in the Post Anaesthesia Care Unit and at 24 hours & 48 hrs postoperatively. A variety of secondary outcomes are being measured including potassium levels, strong-ion-difference, renal biomarkers, requirements for postoperative dialysis, adverse events and hospital stay. (days). We have completed recruitment of 20 patients with a total of 50 participants expected. There are no results at this early stage.

The department of anaesthesia and intensive care have an established research infrastructure and have participated in a number of large scale studies leading to a number of recent NEJM publications.

### **CHEST Study and SAFE Studies**

Of note, the Austin Hospital contributed substantially to the 7000-patient RCT comparing saline (0.9%) to the colloid hydroxyethyl starch for fluid resuscitation in intensive care, which was recently published in the NEJM. In addition, the ICU at Austin Hospital was a major recruiting centre for the multicenter, randomized, double-blind SAFE trial that compared the effect of fluid resuscitation with albumin or saline (0.9%) on mortality in a heterogeneous population of patients in the ICU. This has been one of the most widely cited fluid intervention studies in the world.

**The SPLIT Study: Saline (0.9%) vs. Plasma-Lyte® 148 Fluid Intervention Trial in Major Surgery Patients, Version 3, 1st Oct 2014**

### 1.11 Summary

The demographic, illness severity and outcome data that will account for the majority of data used in this study are already being collected. Existing data suggest that our study will have ample statistical power to establish whether using saline as the default resuscitation fluid increases the risk of acute kidney injury in adult major surgery patients compared to Plasmalyte. The statistical team at the Australian and New Zealand Intensive Care Research Centre, who will conduct the statistical analyses, are familiar with the data being used in the study.

Baxter Pty will provide blinded study fluids for this study. In short, this study has a very high chance of success. It should provide high quality pilot data for a subsequent pivotal, NHMRC-funded, double-blind randomized multicentre pragmatic interventional trial that will inform clinical practice around the world.

## OBJECTIVES

The overall objective of this study is to establish the feasibility, safety and relative biochemical and physiological efficacy of using saline (0.9%) vs. Plasmalyte solution as the primary fluids in adult major surgery patients.

The choice of non-crystalloid fluid intervention such as colloids, or any other blood product e.g. red blood cells, platelets, cryoprecipitate, frozen plasma, bicarbonate, dextrose etc. will be entirely at the discretion of the all clinicians caring for the patients

Specifically, we aim to establish the effect of saline (0.9%) and Plasmalyte solution on:

1. The development of acute kidney injury in hospital
2. The development of biochemical and acid-base derangements
3. The development of postoperative complications
4. Requirements for renal replacement therapy
5. Requirements for mechanical ventilation
6. Hospital length of stay
7. Hospital mortality

## STUDY DESIGN

### 1.12 General

This study is a single-centre pilot prospective pilot study comparing saline (0.9%) and Plasmalyte solution for all perioperative crystalloid fluid therapy in adult major surgery patients.

### 1.13 Inclusion criteria

- Patients aged  $\geq 18$  years admitted to the Austin Hospital who receive major surgery. For the purpose of the study, major surgery will be defined as any surgery requiring overnight post-operative hospital stay.

### 1.14 Exclusion criteria

- Patients who are  $< 18$  years in age
- Patients who are expected to be discharged from hospital on the day of surgery (day surgery cases)
- Raised intracranial pressure (these patients may specific fluid intervention strategies to prevent further increases in intracranial pressure)
- Patients undergoing liver transplantation (these patients require non-lactated crystalloid solutions as part of the Austin Hospital perioperative fluid intervention protocol.
- Patients undergoing renal transplantation, as these patients are currently part of a current randomised clinical trial.

### 1.15 Baseline data

The following baseline data will be collected:

- Age
- Gender
- Admission type (elective vs. emergency)
- Type of surgery (hepatobiliary, colorectal, upper GI, orthopaedic etc.)
- If admitted to ICU: Chronic APACHE co-morbidities (including long-term dialysis)
- If admitted to ICU: APACHE-III admission diagnosis
- If admitted to ICU: Illness severity based on the on the APACHE-III risk of death score
- Baseline creatinine.
- Baseline biochemistry

**(Note: - all of these data are routinely collected for quality assurance purposes or as measured as part of usual clinical care)**

### 1.16 Study treatments

This study is designed to compare two approaches to fluid therapy. It will compare use of Saline (0.9%) or Plasmalyte as the primary default crystalloid fluids.

Blinded study fluid will be provided by Baxter Pty in indistinguishable 1000ml bags. Open label fluids will be available for use in rare situations where the treating clinician believes that there is an indication for one fluid or the other. This may occur, for example, in the setting of severe acidosis where the higher chloride content of saline may make this fluid undesirable because it may increase the risk of more severe acidosis.

**The SPLIT Study: Saline (0.9%) vs. Plasma-Lyte® 148 Fluid Intervention Trial in Major Surgery Patients, Version 3, 1st Oct 2014**

Anaesthetists and surgeons, and intensivists, as well as all clinicians at Austin Hospital have indicated that they regard the study fluids as equally acceptable in essentially every clinical setting in which crystalloid fluid therapy is required. Irrespective of which study fluid the patient receives they will be analysed on an intention to treat basis.

The overall volume of study fluid and any open label study fluid administered as fluid boluses will be recorded daily.

### **1.17 Treatment allocation**

Patients will be randomly assigned, in alternating 6 weeks blocks to use either blinded Saline (0.9%) or Plasmalyte solution. There will be a three week wash-in period and a three-week wash-out period between each fluid intervention.

For example, assume:

**GROUP ONE:** Saline (Blinded)

**GROUP TWO:** Plasmalyte (Blinded)

Three weeks prior to commencement, blinded Saline will be introduced into all theatres, ICU and surgical wards for a 3 week wash-in period. **GROUP ONE** subjects will then receive Saline (blinded) for 6 weeks. This will be followed by a 3-week wash-out period of Saline (blinded). Plasmalyte solution (blinded) will then be washed-in for 3 weeks. **GROUP TWO** subjects will then receive Plasmalyte solution (blinded) for a 6 week period. Plasmalyte solution (blinded) will be washed-out for 3 weeks and the study will stop.

Total study duration: 24 weeks

Any patients who remain in hospital throughout the transition period will continue to receive the blinded fluid that they were originally assigned to for all postoperative crystalloid intervention. Thus blinded fluid will be made available as the only crystalloid fluid in all surgical wards and in the intensive care unit. No controls will be placed on the use of colloidal fluid therapy, blood products (red blood cells, platelets, cryoprecipitate or fresh frozen plasma, or any other fluid non-crystalloid fluid intervention e.g. dextrose, bicarbonate.

## TREATMENT SCHEME

Options will vary depending on final randomisation. Assume:

**Group 1: Plasmalyte (Blinded)**

**Group 2: Saline (0.9%) (Blinded)**

[figure not shown]

## Outcome measures

### 1.17.1 General

The outcome measures are aligned with those used in a recently published open-label sequential period study of chloride liberal vs. chloride-restrictive fluid administration study published in JAMA.

**The SPLIT Study: Saline (0.9%) vs. Plasma-Lyte® 148 Fluid Intervention Trial in Major Surgery Patients, Version 3, 1st Oct 2014**

### 1.17.2 Primary outcome measure

The primary outcome measure will be the proportion of patients with either acute kidney injury or failure based on creatinine levels in accordance with RIFLE-criteria during the index hospital admission.

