| Hospital:            | Austin Hospital                                                                                                                                                                                                                                                                                                                                         |
| Study question:      | Of the commonly used perioperative crystalloid solutions: Saline (0.9%) and Plasmalyte, which solution has the most favourable effect on kidney injury, serum electrolyte levels, and complications in patients undergoing major surgery                                                                                                                |
| Study Objectives:    | To determine the safety and efficacy of using Saline (0.9%) or Plasmalyte solution as fluid therapy in adult patients undergoing major surgery                                                                                                                                                                                                          |
| Primary outcome:     | Acute kidney injury or failure (RIFLE-criteria)                                                                                                                                                                                                                                                                                                         |
| Secondary Outcomes:  | Serum creatinine
Chloride levels
Acid base disturbances
Post-operative complications
Requirements for ICU
Duration of ICU stay
Hospital length of stay
In-hospital mortality                                                                                                                                                       |
| Inclusion criteria:  | Adult patients > 18 years
Elective or emergency surgery
Requiring at least one overnight stay                                                                                                                                                                                                                                                     |

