### 1.7 Study design

This study aims use an interventional design to provide high quality pilot data in a rapid time frame to address this important question and to help decide whether a pivotal randomized controlled trial is justified. Thus, all patients undergoing surgery at Austin Hospital will be randomly assigned to receive either Saline (0.9%) or the balanced crystalloid solution Plasmalyte as the primary crystalloid fluid in a blinded fashion during two study periods.

**The SPLIT Study: Saline (0.9%) vs. Plasma-Lyte® 148 Fluid Intervention Trial in Major Surgery Patients, Version 3, 1st Oct 2014**

The study will be conducted over a 4-month period allowing two interventional periods of 6 weeks each, with a three week wash-in and a three week wash-out period for each group. Blinded study fluid will be used for all crystalloid therapy in all participants. Austin Hospital staff specialists in anaesthesia agree that on the basis of current evidence, Saline (0.9%) and Plasmalyte are equally acceptable for crystalloid fluid therapy in every situation requiring major surgery with the exclusion of surgery for liver transplantation, renal transplantation and patients with raised intracranial pressure, where specific hospital perioperative fluid protocols are used in these settings.

Both Saline (0.9%) and Plasmalyte will be available for open-label administration in the rare situations, where, in the opinion of the treating anaesthetist or clinician, there is a clinical indication for one fluid or the other. This may occur, for example, in the setting of severe acidosis where the higher chloride content of saline may make this fluid problematic because it may increase the severity of such acidosis.

All adult patients who receive blinded or open-label fluid during one of the two-month study blocks will be analysed. The primary outcome will be the proportion of patients with kidney injury or failure based on established criteria. Secondary outcomes will include delta creatinine (the difference between baseline and peak creatinine), serum electrolyte levels, bicarbonate level, requirement for renal replacement therapy, complications and in-hospital mortality.

All of the data required for this study are collected routinely as part of standard clinical care and/or quality assurance activities.

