### 1.17.3 Secondary outcome measures

Secondary outcomes will be

- the incidence of acute kidney injury based on creatinine according to risk, injury, failure, loss, end-stage (RIFLE) classification in the first 3 days hours after surgery,
- the increase between baseline and peak chloride levels in the first 3 days after surgery
- the development of metabolic acidosis (defined as a base deficit > 2 mEq/L or a bicarbonate level <20 mmol/L) in the first 3 days after surgery
- the development of acidemia defined as a pH <7.3 in the first 3 days after surgery
- Postoperative complications
- Need for and duration of renal replacement therapy,
- Proportion of patients requiring mechanical ventilation
- Need for ICU admission
- ICU and hospital length of stay, and
- ICU and in-hospital mortality

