## STATISTICAL CONSIDERATIONS

### 1.29 Power calculations and sample size

A recently published open label sequential period study of chloride-liberal vs. chloride-restrictive fluid administration demonstrated a reduction in the incidence of injury and failure based on RIFLE criteria from 14% (95% CI, 11% - 16%) to 8.4% (95% CI, 6.4% - 10%);  $P < 0.001$ ) with the introduction of a chloride-restrictive fluid regime.

Assuming that, as we have conservatively estimated, we can study 2000 subjects over a 24 week period, our sample size will provide more than 80% power with an alpha of 0.01 to detect a difference of this magnitude.

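### The primary outcome is scored on creatinine alone, so a patient who starts acute renal replacement therapy before reaching the RIFLE injury threshold can count as having no kidney injury

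*Protocol*

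**What the plan says.** Section 1.17.2 defines the primary outcome as the "proportion of patients with either acute kidney injury or failure based on creatinine levels in accordance with RIFLE-criteria", assessed "during the index hospital admission". The first secondary outcome in section 1.17.3 carries the same restriction over the first three days: "the incidence of acute kidney injury based on creatinine according to risk, injury, failure, loss, end-stage (RIFLE) classification".

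RRT is kept apart from both. It is an objective ("Requirements for renal replacement therapy"), it is among the secondary outcomes previewed in section 1.7, and section 1.17.3 lists "Need for and duration of renal replacement therapy" as an outcome of its own.

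The synopsis and section 1.7 describe the primary outcome more loosely, by RIFLE or by established criteria, and neither adds a rule for RRT. Nowhere does the protocol count the start of acute RRT as kidney failure or say how creatinine measured after that start is to be used.

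**The concern.** Creatinine stops measuring native kidney function once RRT begins, because the treatment clears it. If RRT starts while creatinine is still below the injury threshold, later values may never cross that threshold. The patient then has one of the gravest renal courses in the trial and is scored as free of kidney injury. The same patient is an event for the RRT secondary outcome, so the two renal outcomes disagree about the same person.

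The long assessment window does not help, since the values after RRT starts are the distorted ones. Patients who crossed the threshold before RRT began are counted correctly and are not at issue. Nor are patients already on maintenance dialysis, who have not started acute RRT.

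What is at stake is the validity of the endpoint. The affected patients are few but severe, and an imbalance between arms would distort the primary relative risk. The Background and Rationale section says outcome data from this pilot will feed power calculations for a pivotal trial, so the definition could carry forward.

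**Working it through.** **1. Reproduce the stated power.** Inputs: 14% and 8.4% and alpha 0.01 (section 1.29); about 1000 patients per group (section 1.10). Sidedness is not stated; two-sided is used here.

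- Mean rate = (0.14 + 0.084)/2 = 0.112.
- SE under no difference = √(2 × 0.112 × 0.888/1000) = 0.0141.
- SE under the alternative = √((0.14 × 0.86 + 0.084 × 0.916)/1000) = 0.01405.
- z = (0.056 − 2.576 × 0.0141)/0.01405 = 1.40, so power = 91.9%.

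One-sided power is 95.1%, and two-sided power with continuity correction is 90.8%. The claim of more than 80% reproduces.

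**2. How many patients could be missed.** The protocol gives no RRT rate and no RIFLE cut-offs, so both inputs are assumptions: 0.5% to 2% of patients start acute RRT, and 10% to 30% of those start below the injury threshold.

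- Low end: 0.005 × 0.10 × 1000 = 0.5 per 1000.
- High end: 0.02 × 0.30 × 1000 = 6 per 1000.

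At the planning rates there are 140 and 84 events per 1000.

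**3. Direction of bias.** Let the true rates be pS (saline) and pP (Plasmalyte), with fractions mS and mP missed. The observed relative risk is (pP − mP)/(pS − mS). It lies closer to 1 than the true value pP/pS = 0.600 only if mS/mP > pS/pP = 0.14/0.084 = 1.67. Taking 14% and 8.4% as the true rates:

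| Missed, saline vs Plasmalyte | Observed rates | Relative risk | Power, two-sided 0.01 |
|---|---|---|---|
| none | 14.0% vs 8.4% | 0.600 | 91.9% |
| 0.6% vs 0.6% | 13.4% vs 7.8% | 0.582 | 93.3% |
| 0.6% vs 0 | 13.4% vs 8.4% | 0.627 | 84.5% |
| 0 vs 0.6% | 14.0% vs 7.8% | 0.557 | 97.0% |
| 1% vs 0.5% | 13.0% vs 7.9% | 0.608 | 87.6% |
| 2% vs 1% | 12.0% vs 7.4% | 0.617 | 81.7% |

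The last two rows lie outside the assumed range and serve as stress tests. Equal losses move the relative risk away from 1. Losses confined to one arm move it either way, depending on the arm.

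**4. The opposite reading of the planning rates.** Section 1.17.1 aligns the outcomes with the earlier sequential-period study, so 14% and 8.4% may already be creatinine-only rates. Counting RRT then adds patients back.

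- Adding 0.25% to 2% equally to each arm moves the relative risk from 0.600 to between 0.607 and 0.650, and power from 91.9% to between 91.3% and 87.0%.
- Adding 0.5% vs 0.25% (saline vs Plasmalyte) gives 0.597 and 93.6%; 1% vs 0.5% gives 0.593 and 94.9%; 2% vs 1% gives 0.588 and 96.9%.

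Power stays above 80% in every case under both readings.

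**The case against.** The strongest reply is that section 1.30 leaves the full statistical description to an analysis plan that is not at hand, and that the treatment of laboratory values after RRT is ordinary derivation detail. That would be decisive if the protocol were silent. Instead, section 1.17.2 states the basis of classification. A later rule counting RRT as an event would change the stated definition.

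A second reply is that the choice is deliberate, since section 1.17.1 aligns the outcomes with the study that supplied the planning rates. This stands in part: an endpoint with an RRT component may not match 14% and 8.4% exactly. Alignment does not remove the misclassification, however, and a creatinine-only sensitivity analysis keeps the comparison available.

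Third, RRT is reported by arm in any case, so a gross imbalance would be visible. That is true, but it does not correct the primary result.

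A reader might also infer a stronger point: that saline causes acidosis, acidosis prompts early RRT, and the primary relative risk is therefore pulled toward 1. The protocol does not support that chain. Section 1.6 does not mention acidosis. Sections 1.7 and 1.16 say only that saline may worsen severe acidosis, and offer this as an example of when open-label fluid may be used. The Background and Rationale section allows that hyperchloraemic acidosis may be benign. It does cite earlier studies in which a chloride-restrictive strategy or Plasmalyte went with less RRT or dialysis, so RRT overall could be more frequent with saline. Nothing, though, speaks to RRT begun before creatinine has risen, which is the only kind that matters here.

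**Conclusion.** The point holds as a flaw in the endpoint definition. As written, the primary outcome and the 3-day kidney injury outcome can score a patient on new acute RRT as having no kidney injury. This follows from the text and does not depend on where the RIFLE injury cut-off lies.

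Its size is unknown and probably small: 0.5 to 6 patients per 1000 on the assumed rates. No direction of bias can be claimed; it depends on whether the missed fraction with saline exceeds about 1.67 times that with Plasmalyte. One might be tempted to quote a shrinkage of the risk difference from 5.6 to 5.0 points, about 11%. That figure takes the top of both assumed ranges, places every missed patient in the saline arm, and presumes the planning rates are not already creatinine-only, so it is a worst case and not an estimate. Nor is this a power problem, since the stated power reproduces and survives every scenario examined. The change should be made because the misclassified patients are severe cases and the remedy is cheap.

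**What to change.** In section 1.17.2 and the first item of section 1.17.3, state before unblinding that a patient not on maintenance dialysis at baseline who starts acute RRT within the outcome window is classified as RIFLE failure, and that creatinine measured after RRT starts is not used for classification. Report the creatinine-only version as a sensitivity analysis, for comparability with the study behind the planning rates. This concerns only how an outcome is counted, not when RRT should be given.

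Most of the data are already planned: RRT need and duration are listed outcomes, and section 1.21 has study staff collecting the renal outcome data.

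There are three costs. Starting RRT is partly a clinician's decision, so the endpoint is no longer purely a laboratory one. The 14% and 8.4% may not describe the amended endpoint exactly. Finally, section 1.15 records long-term dialysis only for patients admitted to ICU and section 1.14 does not exclude such patients, so maintenance-dialysis status must be recorded for every patient who receives RRT.
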